## Abstract

**Background:**

Despite the well-known importance of cognitive deficits for everyday functioning in patients with severe mental illness (SMI), evidence-based interventions directed at these problems are especially scarce for SMI patients in long-term clinical facilities. Cognitive adaptation Training (CAT) is a compensatory approach that aims at creating new routines in patients’ living environments through the use of environmental supports. Previous studies on CAT showed that CAT is effective in improving everyday functioning in outpatients with schizophrenia. The aim of this study is to evaluate the effect of CAT as a nursing intervention in SMI patients who reside in long-term clinical facilities.

**Methods/Design:**

This is a multicenter cluster randomized controlled trial comparing CAT (intervention group) as a nursing intervention to treatment as usual (control group). The primary goal is to evaluate the effectiveness of CAT on everyday functioning. Secondary outcomes are quality of life, empowerment and apathy. Further, an economic evaluation will be performed. The study has a duration of one year, with four follow-up assessments at 15, 18, 21 and 24 months for the intervention group.

**Discussion:**

There is a need for evidence-based interventions that contribute to the improvement of the functional recovery of long-term residential patients. If our hypotheses are confirmed, it may be recommended to include CAT in the guidelines for SMI care and to implement the method in standardized care.

**Trial registration:**

Nederlands Trial Register (identifier: NTR3308). Date registered: 12 February 2012.

## Background

The term severe mental illness (SMI) defines a range of psychiatric disorders, characterized by serious mental, social and vocational problems that influence each other and create a need for long-term continuous care by mental health professionals [1]. The majority of the SMI population suffers from schizophrenia or related psychotic disorders, which are characterized by positive symptoms (such as hallucinations and/or delusions), negative symptoms (such as amotivation, social withdrawal and/or blunted affect) and cognitive deficits (such as planning, memory and/or attention issues). Furthermore, people with autism, obsessive compulsive disorder, personality disorder, bipolar disorder or major depression are also considered to be suffering from SMI when they follow a severe course of the illness [1]. In the Netherlands, patients with SMI are admitted to long-stay facilities when they are unable to live independently and need more support than can be provided at assisted or sheltered living facilities. Based on the most recent estimations, approximately 10% of the adult SMI population is living in long-stay clinical facilities in the Netherlands [1,2]. The degree of care dependency strongly relates to everyday functioning [3], and is predicted by cognitive impairments, common in the majority of SMI patients [4]. Despite the strong relationship between cognition and everyday functioning, evidence-based interventions are scarce, especially for those who reside in long-stay clinical facilities. Two main approaches can be distinguished with regard to interventions for cognitive problems in SMI: restorative and compensatory.

Restorative approaches, such as cognitive remediation, aim to improve functional outcomes through enhanced cognitive functioning. In cognitive remediation, people are typically trained using computer training software. Cognitive remediation techniques have been extensively studied and though they attain small positive effects on cognition, recent (meta-analytic) studies demonstrated that these improvements do not generalize to functional improvements [5,6]. Significant and larger effect sizes are achieved when cognitive remediation is combined with some form of rehabilitation program, which questions the specific therapeutic effects of cognitive remediation programs on global and real-world functioning [5,6].

Compensatory approaches do not aim to improve cognitive functions per se. Instead, they aim to bypass the cognitive deficits that hinder patients in performing their activities of daily living. Cognitive adaptation training (CAT) is such an approach [7,8]. CAT is an in-home intervention that targets real-world problems in a real-world setting, namely the patient’s own living environment. With the use of environmental supports, the patient is taught new routines that appeal less to cognitive functions. Furthermore, CAT interventions are strongly individualized, taking into account the specific problems in activities of daily living of the individual patient. Effects of CAT include improvements in everyday functioning, quality of life, medication adherence and relapse in outpatients with schizophrenia [7-9].

CAT starts with composing an individually tailored treatment plan, based on the patient’s specific problems with respect to behavior, cognitive or executive functioning and everyday functioning. If the patient’s behavior type is predominantly characterized by apathy (amotivation, lack of initiative and/or lack of goal-directed behavior), compensation strategies will focus on cueing and prompting behavior. Patients whose behavior is predominantly characterized by disinhibition (easily distracted by irrelevant stimuli and/or behaving inappropriate in a situation) may benefit from removal of distracting stimuli. For patients with a mixed behavior type, both intervention strategies can be used. The form of the intervention is based on the level of executive functioning of the patient (such as planning, goal-directed behavior and mental flexibility). Interventions for patients with poor executive functioning are more easily noticeable (for example, larger signs), more specific (for example, stepwise instructions) and more numerous, compared to interventions for patients with fair executive functioning, which can be more subtle (for example, smaller signs) and less specific (for example, global instructions).

Information about the patient’s cognitive strengths and weaknesses in attention and memory is used to further individualize the interventions. For example, if a patient has strong visual attention but their auditory attention is weak, they would probably benefit more from visual cues and/or signs than from verbal reminders. The specific individual problems in everyday functioning determine the individual goals at which the interventions are directed. Commonly used environmental supports are watches, calendars, electronic devices, signs, household supplies (such as boxes and cleaning supplies) and means of transportation (for example, the bus or a taxi pass). A CAT manual includes examples of specific environmental supports for 16 domains of daily living [10], and was slightly adapted (by authors APMS and PQ) for practical use by psychiatric nurses.

Despite the well-established effectiveness of CAT for outpatients, it remains unclear whether long-term residential patients can benefit from CAT in a similar way. In this population, the cognitive and functional deficits can be considered to be most severe. Therefore, CAT may bridge the gap between the current knowledge about these deficits and the lack of evidence-based interventions for this patient group. At the same time, long-stay facilities may be better able to deal with the need for ongoing support, which is necessary to maintain the functional improvements made with CAT [9,11].

In the usual care of long-stay facilities, ongoing support is often provided by psychiatric nurses. Supporting patients in performing everyday tasks is part of their daily working routine. While in previous studies CAT was delivered by psychologists with a minimum of a bachelor’s level education, the current study aims to train psychiatric nurses for CAT. Involving nurses should integrate CAT in the daily working routine and thereby provide the continuous support which is necessary to sustain improvements that are made with CAT. A pilot study conducted by our group provided tentative evidence that CAT as a nursing intervention can improve everyday functioning in long-term residential patients in the Netherlands [12]. Furthermore, a recent Canadian study demonstrated that case manager support can sustain CAT interventions after a period of CAT-specialized intervention [13].

The abovementioned studies only included patients with a diagnosis in the schizophrenia spectrum, which leaves the effect of CAT on SMI patients with a different diagnosis unknown. However, cognitive impairments are also present in patients with other psychiatric disorders [14]. Therefore we expect that SMI patients with cognitive deficits, but without the psychotic symptoms that characterize schizophrenia, may similarly benefit from CAT.

The primary goal of the current study is to assess the effect of CAT as a nursing intervention on everyday functioning in long-term residential patients with SMI. The secondary goals are to evaluate the effect of CAT on quality of life, empowerment and apathy. Follow-up measurements will be conducted to evaluate whether obtained effects on primary and secondary outcome measures can be retained, as well as to evaluate the feasibility of integrating CAT support into the daily working routine of the nurses. We expect CAT as a nursing intervention to lead to improvements in everyday functioning and apathy, and thereby an improved quality of life for patients with SMI. As CAT is not designed to alter cognitive functioning (rather to bypass cognitive problems) or to improve positive symptoms, we do not expect these to change. Finally, we will assess the long-term cost-effectiveness and cost-utility of the intervention. Importantly, in a time where available funding for mental healthcare is diminishing, evaluation of the costs and benefits of CAT is necessary. With this information available, mental health institutions will be able to make well-considered decisions with regard to the type of treatments and interventions that they offer.

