### Design

This is a two-arm, multicenter, cluster randomized controlled trial assessing CAT as a nursing intervention in long-term residential patients with SMI. Patients in the intervention group will receive CAT in addition to treatment as usual ((TAU) CAT + TAU) and will be compared to the control group who will only receive TAU. Assessments take place at baseline and every three months thereafter. This study has a duration of one year. For the intervention group, four additional assessments take place at 15, 18, 21 and 24 months in order to investigate the long-term effects.

The Medical Ethics Review Committee of the University Medical Center Groningen in the Netherlands approved the study design, research protocol, information brochure and informed consent procedure (approval number M13.143271). The study is funded by a NutsOhra grant (grant number: 1303–041).

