### Tests and measures

#### Testing procedure

All participants (intervention and control group) are measured at baseline and after three, six, nine and 12 months. Additionally, to determine whether any obtained results in the intervention group can be retained, follow-up assessments are planned after 15, 18, 21 and 24 months. Although CAT is not designed to alter cognitive functioning (rather to bypass cognitive problems) nor to improve symptoms, cognitive functioning and symptomatology are measured again at six and 12 months to evaluate any unexpected changes. The schedule of enrollment, interventions and content of the assessments is shown in Table 1. For all patients, interviews and cognitive tests are assessed in separate sessions. In the intervention group, environmental and functional problems in everyday functioning are assessed in an additional session. Level of everyday functioning is chosen as the primary outcome. All tests and measures are described below. Secondary outcome measures are quality of life, empowerment and apathy. Assessment outcomes for the control group will not be used in their treatment plan for the duration of the trial.

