**Assessments:**										
Environmental/functional problems^b^ and behavior type		X								
Clinical and cognitive characteristics		X		X		X				
Demographical information		X								
Everyday functioning		X	X	X	X	X	X	X	X	X
Quality of life and empowerment		X		X		X				
Apathy		X		X		X				
Healthcare costs		X	X	X	X	X	X	X	X	X

^a^Number illustrates number of months after baseline.

^b^Assessed for the intervention group only.

^c^
*Abbreviations*: *TAU* treatment as usual, *CAT* Cognitive Adaptation Training.

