#### Healthcare consumption and costs

This study is conducted from a healthcare perspective, since costs within the healthcare system are most relevant for the current study population. Medical costs that will be assessed include costs of the interventions (costs of personnel, materials and housing), inpatient care and medication use. In order to calculate costs, Dutch standard prices for each cost unit [37] are combined with information on healthcare consumption. Healthcare consumption will be prospectively registered for all the included patients by means of a detailed questionnaire adapted to the context of the current study. This questionnaire is completed by each CAT case manager at baseline and at three, six, nine and 12 months for both groups and at 15, 18, 21 and 24 months for the intervention group.

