## Discussion

In SMI care, especially in the chronic stage of the disease, there is a necessity for practical hands-on interventions that target the functional impairments resulting from cognitive deficits in such a way that functional improvements are made, and can also be sustained after a study period. Primarily the latter aspect made us choose an intervention that can be applied by those healthcare professionals who support patients in their daily routine, namely psychiatric nurses. The current, multicenter, cluster randomized controlled trial meets with these needs by assessing the efficacy of CAT as a nursing intervention on everyday functioning in residential patients with SMI. We hypothesize that CAT as a nursing intervention leads to improvements in everyday functioning (primary outcome) and apathy, and thereby in quality of life and empowerment (secondary outcomes).

A strength of this study is that patients are recruited from multiple psychiatric institutions spread across the Netherlands, increasing representativeness and thus increasing generalizability. An additional strength is that it addresses the long-term effects of the intervention (up to two years). The length of the study takes into account that rehabilitation in long-term residential patients is a slow process [39]. Furthermore, by following up on everyday functioning for up to two years (one year after completion of the study), we will evaluate whether CAT has been successfully incorporated in the working routine of nurses. This is important because the nurses will have to provide ongoing support to sustain improvements. Another strength is that the outcomes of everyday functioning are not solely based on self-reports, but are also assessed by the number of work-related activities per week, and by observational questionnaires that are filled out by the CAT case manager. As such, we use various measures to substantiate our impression of the level of everyday functioning of the patients. Furthermore, this approach allows us to collect data even if the patient misses an assessment. Finally, because of our choice not to hold common eligibility criteria, for example with regard to diagnosis or (prior) comorbid psychiatric or somatic disorders, our results will be better generalizable to the whole SMI population, instead of only pertaining to schizophrenia patients. This is important since it increases the clinical importance and external validity of our findings.

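### Long-term cost-effectiveness and retention of secondary outcomes are promised, but after 12 months there is no control arm and no quality-of-life, empowerment or apathy assessment

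*Protocol article*

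**What the plan says.** **Aims.** The Background section of the protocol article promises, for the economic part: "Finally, we will assess the long-term cost-effectiveness and cost-utility of the intervention". For the follow-up it says: "Follow-up measurements will be conducted to evaluate whether obtained effects on primary and secondary outcome measures can be retained".

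**Meaning of long-term.** Under Design, the study itself lasts one year, and the later visits are given this purpose: "For the intervention group, four additional assessments take place at 15, 18, 21 and 24 months in order to investigate the long-term effects". The Discussion lists as a strength that "it addresses the long-term effects of the intervention (up to two years".

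**Schedule.** Table 1 has control patients at months 0, 3, 6, 9 and 12 and marks the follow-up columns as applying to the intervention group only. The row headed "Quality of life and empowerment" is ticked at months 0, 6 and 12, and so is the apathy row. Only everyday functioning and healthcare costs are ticked after month 12. Under Healthcare consumption and costs, the cost questionnaire is completed at baseline and "at three, six, nine and 12 months for both groups and at 15, 18, 21 and 24 months for the intervention group".

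**What is to be estimated.** The section Economic evaluation compares CAT plus usual treatment with usual treatment alone. The cost-effectiveness result is incremental cost per MCAS point, and the QALYs come from SF-12 utilities. In the statistical section, the treatment effect at each time point is the intervention mean minus the control mean.

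**The concern.** The aims reach further than the data. Each economic quantity the article defines is a difference between arms, and one arm stops halfway through the 24 months. The cost-utility analysis has a second gap: its only source of utilities, the SF-12, stops at month 12 even in the arm that is followed.

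A separate conflict sits in the retention aim. It names the secondary outcomes, which the article defines as quality of life, empowerment and apathy, but none of them is measured in the period in which retention would be judged.

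What is at stake is the meaning of the analysis planned at 24 months. The Background says that institutions will use the economic results to choose which treatments to offer. A stable course among the intervention patients still being assessed could be reported as a lasting effect or as long-term value for money, although the trial cannot show what would have happened under usual treatment over the same months.

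**Working it through.** The point rests on the schedule, so the check lists which time points carry data in which arm. Inputs are Table 1 and the section Healthcare consumption and costs.

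| Measure | Both arms (months) | Intervention arm only (months) |
|---|---|---|
| Everyday functioning (incl. MCAS) | 0, 3, 6, 9, 12 | 15, 18, 21, 24 |
| Healthcare costs | 0, 3, 6, 9, 12 | 15, 18, 21, 24 |
| SF-12 and empowerment | 0, 6, 12 | none |
| Apathy | 0, 6, 12 | none |

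**Step 1: comparative visits after month 12.** Four visits are planned (15, 18, 21, 24). Control patients attend 0 of 4. The longest period with a randomised comparison is 12 of the 24 months.

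**Step 2: cost-effectiveness.** The ratio is (cost in CAT − cost in TAU) / (MCAS change in CAT − MCAS change in TAU). For months 12 to 24 both TAU terms are unobserved, so neither numerator nor denominator can be formed from trial data.

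**Step 3: cost-utility.** Assume the usual area-under-the-curve method, which the article does not spell out, with utilities u0, u6 and u12. Year-one QALYs per patient are 0.5 × (u0 + u6)/2 + 0.5 × (u6 + u12)/2 = 0.25·u0 + 0.5·u6 + 0.25·u12. All three terms are collected in both arms, so year one can be computed. Year two needs at least one utility after month 12, and there are none in either arm. Carrying u12 forward would give 1 × u12, which is an assumption and not an observation.

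**Step 4: retention.** Retention of an outcome needs at least one measurement after month 12. Everyday functioning has four, in the intervention arm. Quality of life, empowerment and apathy have 0 of 4.

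**Step 5: blinding after month 12.** Only intervention patients are seen from month 15, so the visit date alone reveals the arm to a rater who knows the schedule. The allocation guess made after each assessment has no control patients to set against it from then on, so it cannot separate real knowledge of the arm from a general tendency to guess CAT.

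No part of this depends on the sample-size calculation, and no figure there changes.

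**The case against.** **The follow-up is openly described as intervention-only.** This stands in large part. Testing procedure gives its purpose: "to determine whether any obtained results in the intervention group can be retained, follow-up assessments are planned after 15, 18, 21 and 24 months". Sample size calculation separates an analysis of both groups at 12 months from one at the end of intervention-group follow-up. The Discussion links the second year to whether nurses have taken CAT into their routine. A reader might infer from *long-term effects* that a between-group effect at 24 months is planned. The documents do not support that: the treatment effect is defined as a difference from control and so exists only where controls are measured. But this disclosure does not rescue the economic aim, which is comparative by its own definition, nor the retention aim for secondary outcomes.

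**No horizon is attached to long-term in the economic sentence.** True. The evaluation runs alongside a study described as lasting one year, and a 12-month horizon may be what is meant. Against this, the article elsewhere uses *long-term* for the period up to two years and collects intervention-arm costs to month 24. It describes no model or extrapolation that would bridge the gap.

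**An article condenses.** The schedule has not been left out. It is printed, and it conflicts with the printed aims.

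**Blinding.** A reader might infer that every rater after month 12 certainly knows the arm. The documents do not show this. Under Blinding, raters receive no information on the content or aims of the intervention, and nothing says whether they know that only CAT patients continue. Nor does the risk concern every functioning measure: the SFS and LSP are completed by the CAT case manager in the intervention arm, and work activity is registered by staff, so these have no blinded 12-month scores to lose.

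**Conclusion.** The concern holds. As written, the article claims something the design does not have: a long-term comparative economic evaluation, and a test of whether secondary outcomes are retained. After month 12, incremental costs and incremental MCAS have no comparator, QALYs cannot be computed in either arm, and retention of quality of life, empowerment and apathy cannot be assessed. An uncontrolled within-arm course of everyday functioning and costs can be described, but it cannot be attributed to CAT. Loss of rater blinding after month 12 is a risk, not an established fact, and the conclusion does not depend on it.

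Severity is moderate. It would be tempting to conclude that the economic evaluation fails altogether, but the documents do not support that. Both arms have costs and MCAS at 0, 3, 6, 9 and 12 months and the SF-12 at 0, 6 and 12, so the 12-month effect, cost-effectiveness and cost-utility analyses are unaffected.

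The conclusion assumes that *long-term* in the economic aim means what it means in Design and Discussion, a period beyond 12 months. If 12 months is meant, the economic part reduces to an unclear word; the conflict over secondary outcomes remains.

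**What to change.** - **Background, economic aim:** state a 12-month horizon for the cost-effectiveness and cost-utility analyses and delete *long-term*. Any longer horizon should be a declared model extrapolation with its assumptions stated.
- **Background, retention aim:** limit it to everyday functioning, removing the secondary outcomes.
- **Design and Discussion:** describe months 12 to 24 as an uncontrolled within-group course in the intervention arm, and say that it does not support a between-group effect. Note there that visit timing can reveal the arm to raters who know the schedule.

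This changes wording only: no extra data, and no change to sample size or to the 12-month analyses. The price is that the long-term claim is given up.

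Keeping the claim would require data that are not now scheduled: control-arm MCAS and costs to month 24, the SF-12 in both arms after month 12, and, for the retention aim, empowerment and apathy after month 12. That is a much larger change.
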